## Abstract

**Background:**

Youth in the United States are experiencing rising rates of anxiety, depression, and other mental health challenges, yet many remain underserved due to systemic barriers such as poverty, limited access to care, and shortages in the mental health workforce. Schools and primary care clinics are trusted, community-based settings that offer strategic opportunities for early identification, prevention, and intervention. As part of a public health approach, integrating digital mental health tools into these settings can support broad access, enhance mental health literacy, and promote help-seeking behaviors among all students. When co-designed with youth and embedded within existing care systems, these tools offer a scalable, proactive solution to support well-being across diverse school-aged populations.

**Objective:**

This protocol describes the design and implementation of a stepped-wedge clinical trial to evaluate the Connected for Wellness mobile app, a youth- and caregiver-facing digital mental health intervention. Developed using participatory informatics and human-centered design principles, the app provides culturally relevant content in English and Spanish. Features include self-guided wellness activities, well-being screeners, psychoeducational videos, and localized service directories. Machine learning algorithms personalize content recommendations based on user inputs and behavioral patterns.

**Methods:**

This trial uses a stepped-wedge cluster randomized design across 20 community-based sites (10 high schools and 10 primary care clinics) in 2 counties in California. These counties were selected for their high proportions of underserved youth populations. All youth aged 13 to 22 years and their caregivers will be invited to access the app. Sites are randomized into 2 implementation waves. The app is introduced site-wide as a universal public health intervention supported by on-site navigators and peer ambassadors. The primary outcomes are derived from a cascade-of-care framework, including identification of mental health need, referral to services, initiation of services, and engagement (defined as ≥3 treatment visits). Data will be collected via anonymous in-app analytics, monthly World Health Organization–Five Well-Being Index assessments, and deidentified electronic health and administrative records. Generalized linear mixed models will be used to evaluate differences in cascade outcomes between pre- and postimplementation phases while accounting for clustering and site-level variability.

**Results:**

As of May 2025, the mobile app has been finalized, institutional review board approvals have been secured, and all study sites have been recruited. Participant recruitment is projected to begin in August 2025. Data collection and initial analyses will begin in early 2026, with preliminary findings expected by October 2026.

**Conclusions:**

This study tests a novel digital health intervention integrated into trusted care systems. If effective, the Connected for Wellness mobile app may serve as a scalable strategy to reduce disparities in mental health care access and engagement for youth across the United States.

**Trial Registration:**

ClinicalTrials.gov NCT06122688; https://clinicaltrials.gov/study/NCT06122688

**International Registered Report Identifier (IRRID):**

PRR1-10.2196/73721

## Introduction

### Background

Could a mobile mental health app designed for youth and caregivers help address mental health service barriers? For decades, research has documented the ongoing and persistent inequities in mental health care access for many populations, including both rural and urban [1-3]. Innovative aspects of the clinical trial protocol reported in this paper include using a mobile app codeveloped with youth and families through participatory informatics to drive technological innovation considering youth and caregiver priorities regarding customizable features and in-app resources.

Our previous work supports the hypothesis that mobile apps and other digital health interventions are effective for delivering mental health and prevention services provided that they meet the needs and preferences of end users [4]. These interventions can be successfully implemented within child-, adolescent-, and family-serving systems of care. Unlike clinicians’ time, technology offers a nonconsumable strategy (ie, available asynchronous content vs scheduled therapist time) for improving mental health care access [5]. The United States has witnessed an increasing need for youth mental health services, especially for stress-related challenges [6,7] and populations disproportionately affected [8]. National data reveal that, after controlling for sociodemographics, severity of symptoms, income, and health insurance, Black and Latino youth with similar needs as White youth were almost half as likely to receive mental health services [3].

Barriers to care exist across multiple levels, including cultural, community, family, and systemic factors. For instance, Latino caregivers may perceive children’s behavioral challenges as issues to address within the family, struggle with the lack of linguistically and culturally appropriate services, or experience stigma and perceptions of mental health needs that differ from those of mental health care providers [9]. Rural communities of all backgrounds are also underserved. These systematic factors contribute to reduced use of mental health services even in high-risk populations, underscoring the need for focused interventions that can both help mental health symptoms and risks and promote and facilitate engagement with services [10].

Mobile app interventions, integrated into trusted community settings such as schools and primary care clinics, offer scalable solutions to improve access to youth mental health care. To be effective and acceptable, apps need to include features and content that are designed to be engaging for and address the needs of diverse groups [11]. Despite the proliferation of digital health interventions for youth across a range of delivery methods (eg, websites, apps, games, robots, and virtual reality) [12], few are co-designed with the intended users in mind [13]. Furthermore, the methods used for youth and caregiver collaboration in the design process vary widely [14]. This is unfortunate as studies have demonstrated high levels of acceptability among youth for engaging with mobile health app interventions [15]. These tools can be important nonconsumable and scalable approaches for delivering mental health prevention and wellness tools [16]. When mobile mental health apps are used to expand access to mental health education and prevention resources, youth may be more likely to initiate and engage in help-seeking behaviors, and families may report greater satisfaction with care and perceive services as more appropriate once they engage [17].

Accessibility to mobile apps is another important consideration [18,19]. Use of cross-platform frameworks such as React Native [20] can ensure that an app is easily available to a wide community of users while retaining a single codebase for agile development. Mobile apps can also be integrated effectively with school-based and primary care services. Schools and primary care clinics are critical health care and mental health service providers [21], especially for underresourced populations [22]. Pediatric primary care is widely recognized as an important setting for identifying and managing youth mental health needs given that most youth make at least one medical visit annually [23]. In addition, access to mental health supports has often been expanded through educational settings [24], including the adoption of whole-school, multitiered systems of support that provide school-wide preventive interventions and mental health services through school-based health clinics and programs [25].

### Overview of the Connected for Wellness Mobile App

In an effort to address the barriers to care for youth, a co-designed mobile app called Connected for Wellness was created with adolescents and their caregivers. The development of the Connected for Wellness mobile app and its predecessor, Connectd for Schools [26], is grounded in participatory informatics approaches. *Participatory informatics* [27] is an approach to technology codevelopment that combines best practices from community-partnered participatory research [28] and end user–centered participation in technology design [29]. This approach addresses community health priorities by including intended users as equitable partners throughout the design process. The codevelopment of the Connected for Wellness mobile app with youth and caregivers was led by the scientific team that includes diverse, multilingual research staff, child and adolescent psychiatrists, psychologists, technology development experts, and student researchers. The content includes engaging videos created by and representing diverse youth and caregivers in English and Spanish (details on the codevelopment process and protocols are reported elsewhere). In its final form, Connected for Wellness has four key components: (1) mental health and wellness education, (2) self-assessment tools, (3) emotion regulation and coping strategies, and (4) site-specific and community resources. The home page features a Get Help Now button that directly connects the user to 911 for those who need immediate assistance. The community resources include an embedded link to FindHelp, which is searchable by zip code. In addition to listings of financial assistance and free and reduced-cost food, housing, and health care, FindHelp also features helplines for specific needs such as domestic violence assistance and for communities that are particularly underserved. Given our priority to ensure that the app is widely accessible, we also developed a PDF document that provides all app content for anyone who is using a screen reader or prefers reading along.

The app includes optional notifications, inspirational messages, and interactive components to promote ongoing engagement. In addition, the co-design process led to the development of an app that prioritizes user confidentiality and safety. The app allows for anonymous use, does not include 2-way communication, and avoids open-text response fields, minimizing the risk of exposing sensitive personal information and ensuring that users can engage with the content privately and safely. We collaborated with both English- and Spanish-speaking communities to develop Connected for Wellness content in both languages. Table 1 outlines the app’s features and pathways and includes images of the app’s user interface.

To enhance customization and interactivity for both youth and caregivers, the Connected for Wellness mobile app uses collaborative filtering techniques [26] to intelligently recommend wellness skills and supportive resources to study participants. One approach, a content-based (*item-item*) method, automatically suggests skills based on previously viewed skills and the metadata associated with them. For example, the app clusters content related to similar topics—such as sleep health or emotion regulation—by analyzing descriptions, titles, and other metadata, allowing it to recommend new wellness skills that are semantically similar to those the user has already explored.

In addition, the app uses a peer-based (*user-user*) approach, which identifies users with similar engagement patterns and recommends resources that those similar users have found helpful but the current user has not yet accessed. A second layer of intelligence involves user classification, where youth responses to in-app wellness screeners trigger tailored protocols and personalized content recommendations based on their identified needs. Specifically, Connected for Wellness includes the World Health Organization–Five Well-Being Index (WHO-5) [30], a short questionnaire that measures a person’s well-being over the previous 2 weeks and is suitable for children aged ≥9 years. Users can access this questionnaire on their own and will be reminded to complete it monthly through a notification. Higher scores on the WHO-5 indicate better mental well-being, whereas lower scores indicate potential risk of mental health concerns. After responding to the well-being questions, users receive a well-being score categorized as low, moderate, or high. On the basis of their score, they are provided with personalized well-being activities and suggestions, which can be saved in the app’s Toolbox section for easy access later. For example, a user who scores low on the WHO-5 will receive recommendations for professional help seeking, along with evidence-based strategies to support well-being, such as behavioral activation and emotion regulation techniques. Figure 1 illustrates how the WHO-5 normed scoring system guides the Toolbox recommendations and suggestions for help seeking provided to users based on their check-in results (ie, scores on the WHO-5: green** **for high well-being,** **yellow for moderate well-being, and orange for low well-being).

The primary objective of this study is to evaluate the effectiveness of the Connected for Wellness mobile app in enhancing youth engagement with mental health services when implemented in schools and primary care settings. This study aims to leverage the app’s ability to deliver evidence-based, culturally and contextually relevant information to address key barriers to mental health care, including stigma, limited accessibility, and the need for youth autonomy and confidentiality.

In addition, this study will explore how the app—co-designed with input from both youth and caregivers—enhances engagement with mental health support services and fosters help-seeking behaviors among youth and their families. Our main hypothesis is that the Connected for Wellness app will improve cascade-of-care outcomes compared to usual care. Specifically, we expect that youth at sites implementing the intervention will seek help more often, be screened more frequently, and be more likely to attend at least 3 mental health sessions if identified as needing services. If effective, the app has the potential to be a scalable tool for supporting youth mental health in community-based settings such as schools and primary care clinics and advancing public health approaches to connecting youth with care.

**Table 1 table1:** Features of the Connected for Wellness mobile app for youth and caregivers.

Feature (English and Spanish)	Description	Examples
Pathways [figure not shown]	Brief videos and quick tips on well-being topics	Getting better sleep Improving communication Grief and loss Social connectedness Relaxation Managing emotions Academic stress Mental health help seeking
Self-assessments [figure not shown]	Short questionnaires to gauge sleep and well-being (for youth and caregivers) and social determinant of health needs (for caregivers)	WHO-5^a^ PROMIS^b^ sleep items Social determinant of health questions
Directory [figure not shown]	Site-specific, local, and national resources with direct dial, maps, and information about resources	Hotlines Helplines Clinic- or school-specific mental health and social resources located on-site Community resources (FindHelp)
Toolbox [figure not shown]	Over 500 well-being activities and suggestions that can be saved in the “Toolbox”	Brief suggestions based on well-being frameworks that include domains of physical, psychological, emotional, spiritual, relational, professional, and cultural well-being

^a^WHO-5: World Health Organization–Five Well-Being Index.

^b^PROMIS: Patient-Reported Outcomes Measurement Information System.

**Figure 1 figure1:**
[figure not shown]
World Health Organization–Five Well-Being Index (WHO-5) well-being check-in responses.

## Methods

### Objectives

This study protocol was developed in response to the National Institutes of Health, and the study was funded in August 2023 by the National Institute of Mental Health and will be completed by June 2027. In this section, we present the protocol for implementation of the mobile app using a stepped-wedge design in 10 schools and 10 clinics.

### Stepped-Wedge Design

We use a stepped-wedge design, a type of cluster randomized trial that involves clusters (such as groups of clinics or schools) randomly assigned to different time points (ie, waves) to begin receiving the intervention [31]. The rationale for the stepped-wedge design includes its effectiveness in testing health care delivery models and related outcomes for systems of care, particularly when randomization at the individual level is not feasible [32]. A stepped-wedge design is also ideal when an intervention must be rolled out gradually due to logistical, financial, or ethical constraints, ensuring that all groups eventually receive the intervention. It is particularly useful for evaluating complex, systemic, or behavioral interventions when simultaneous initiation of the intervention is not feasible. Because the goal is to offer the intervention to all youth and caregivers at participating study sites, 2 clusters—consisting of 5 schools and 5 primary care clinics per wave**—**are randomly assigned to 2 different implementation waves. All clusters begin in the control condition, with the Connected for Wellness mobile app intervention introduced to schools and clinics at predetermined time points. By the end of the trial, all clusters will have received the intervention, allowing for a stepped implementation across the sites. Stepped-wedge designs are becoming increasingly popular for testing health care delivery models [33] and are an innovative approach for evaluating the public health impact of mobile apps delivered as universal or tier 1 interventions in youth- and family-serving systems of care [34].

### Setting and Participants

This study will include youth aged 13 to 22 years (to include the range of possible ages in high school) and will be implemented across 10 public high schools and 10 community-based primary care clinics in 2 regions in California, United States. Caregivers will also be invited to use a version of the app for support of their child and their own well-being; however, this study does not monitor caregiver outcomes. Study sites will include urban and rural regions. The investigators will collaborate with one large school district and a network of primary care clinics that are part of a Federally Qualified Health Center system serving desert and rural regions. The schools and primary care clinics have existing peer support leaders or family navigators, who will integrate the Connected for Wellness app into their usual care in supporting students and caregivers in accessing mental health services and resources, encouraging help seeking, and using the in-app wellness skills.

### Recruitment Strategy and Site Selection

Schools and clinics were selected based on (1) geographic (urban and rural) and full demographic representation, (2) service to communities with high proportions of underserved youth (including low-income White, Latino, Black, and Asian backgrounds), and (3) existing collaborations with the investigative team. Sites had to demonstrate adequate infrastructure, including wellness navigators, school-based health centers, or peer educator programs. Recruitment within each site will involve promotional campaigns, informative sessions, videos, and peer navigator outreach.

### Existing Peer-to-Peer and Navigator Models

The high schools partnering with this study have an existing peer-to-peer model in which high school students are trained in a *community health framework* to deliver health and mental health education on topics relevant to their adolescent peers. This model targets health disparities by promoting wellness and reducing barriers to care within a culturally appropriate and community-centered approach [35,36]. Trained students lead school-wide campaigns to promote awareness and education with support from adult allies. In addition, each school has wellness navigators who will play a key role in integrating the mobile app into both school-wide educational efforts and individual support provided to students and caregivers. The primary care clinics participating in this study also have bilingual case managers and family navigators who will promote app use. These support specialists will be partnering with youth and families to help them access mental health information, develop wellness skills, and navigate linkages and referrals to care and community resources through the app.

### Participant Eligibility Recruitment, Consent, and Monitoring

For the study sites, 10 schools and 10 primary care clinics have been recruited to use the Connected for Wellness app site-wide, entering the study in 2 randomized cohorts (see Multimedia Appendix 1 for study timeline). All youth and caregivers at each intervention site will be offered the mobile app. Each site will have a site ID code to access the app. All youth aged 13 to 22 years at the site will be invited to participate in the study by using the mobile app. We will use an information kick-off event, other mental health and promotional events, website links, and videos that provide information about the study. Navigators, site champions, and peer ambassadors will also promote the app and help with downloads for participants requesting help (eg, caregivers who are less comfortable with technology). After all youth or caregivers download the app, they will choose their preferred language (English or Spanish) and role (student or caregiver).

As approved by the institutional review board (IRB) for this study, participants will then complete the in-app consent process, which presents study information in both video and text formats along with comprehension questions to ensure that participants understand the consent process. Only those who answer the questions correctly and indicate their willingness to proceed will gain access to the app. To maximize anonymity—a priority identified during the codevelopment phase—users do not enter any personally identifying information (such as name, email, date of birth, or password). Investigators will regularly review anonymous app data and maintain an aggregated dashboard by site, including demographic characteristics of app users. The dashboard will also capture app use patterns. Using insights from enrollment and app use data, the research team will work closely with school and primary care clinic study champions to actively promote study participation and engagement across the sites.

### Primary Outcomes: Cascade-of-Care Framework

The primary study outcomes are based on the cascade-of-care framework that focuses on population-level health needs and tracks individuals across relevant stages of a health care continuum [37,38]. Originally developed by the Juvenile Justice–Translational Research on Interventions for Adolescents in the Legal System [39,40], the steps in the cascade of care are identification of a behavioral health need, referral to behavioral health care, initiation of services, and engagement with services (>3 visits). The cascade of care has been adapted for youth in foster care [41]; this version was used for this study. Data on each step of the cascade of care will be obtained from deidentified electronic medical records and administrative data at the individual youth level from each of the study sites. This approach, which uses established databases, will enable comparison of cascade-of-care outcomes after implementation to data that were collected before preimplementation years. As detailed in the analytic plan in the Data Analysis section, individual-level data will be aggregated to the site level to test the hypothesis that implementation of the Connected for Wellness mobile app intervention is associated with improvements in youth progression through the cascade of care compared to the (preintervention) control condition. Improvements in the cascade of care are an established public health outcome as they help identify gaps in care and assess the effectiveness of the mobile app intervention. At a population level, in schools or primary care clinics, examining the cascade can inform how well an intervention improves youth access, engagement, and outcomes for a specific population and whether the intervention effectively addresses their unique needs and disparities. Statistical power was determined relative to the current level of each of the cascade outcomes (identification of mental health need, match to services, and initiation of services) in the sites as reflected in administrative data. Power was calculated separately for each cascade outcome. With a power of 0.8, an α value of .05, and 2-tailed tests, the planned design and sample sizes enable detection of small differences between the intervention and control conditions in all the cascade outcomes (2%-10%). Table 2 shows the operational definitions for the cascade-of-care outcome variables, and Table 3 shows the definitions, data collection, and outcomes.

**Table 2 table2:** Cascade-of-care model based on Connected for Wellness triage outcomes.

Step	Rate	Operational definition
Youth at site (step a)	(a)	Total number of youth enrolled at a high school campus or on a patient panel at the primary care clinic site
Need identified (step b)	(b/a)	Subset of total enrolled youth (step a) who complete mental health and social determinant of health needs identification at school or the primary care clinic
Matched to services (step c)	(c/b)	Subset of youth with needs (step b) who receive a referral
Initiated services (step d)	(d/c)	Subset of those referred to services (step c) who initiate services (eg, first treatment session)
Engaged in services (step e)	(e/d)	Subset of those who initiate services (step d) who have ongoing sessions (≥3 visits)

**Table 3 table3:** Primary outcomes based on the cascade-of-care framework and covariates for generalized linear mixed model (GLMM) analysis.

Cascade step	Operational definition and data description	Covariates in GLMM
Need identified	Youth who completed self-assessments or were flagged by navigators	Age, gender, race, ethnicity, site type (school vs clinic), and urban or rural
Matched to services	Referral documented in site records or follow-up logs	All the aforementioned covariates+previous mental health history if available
Initiated services	Attended first mental health appointment	Same as the previous covariates
Engaged in services	≥3 treatment sessions attended	Same as the previous covariates+time since app onboarding

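### Three of the four primary cascade rates (c/b, d/c, e/d) use denominators that the app is expected to change, so they mix its effect with a change in who is counted

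*Protocol article*

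**What the plan says.** The abstract makes all four steps primary: "The primary outcomes are derived from a cascade-of-care framework, including identification of mental health need, referral to services, initiation of services, and engagement". Table 2 then fixes the rates:

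- Step a, the base: "Total number of youth enrolled at a high school campus or on a patient panel at the primary care clinic site".
- b/a: youth at the site who complete needs identification.
- c/b: "Subset of youth with needs (step b) who receive a referral".
- d/c: "Subset of those referred to services (step c) who initiate services (eg, first treatment session").
- e/d: "Subset of those who initiate services (step d) who have ongoing sessions (≥3 visits").

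The Data Analysis section ties the primary hypotheses to the cascade as Table 2 defines it, and predicts improvement on every outcome. It defines no rate c/a, d/a or e/a.

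Both the main hypothesis at the end of the Introduction and the Data Analysis section expect more frequent screening at intervention sites. Table 3 counts a youth as having a need identified through a completed self-assessment or a navigator's flag.

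The engagement hypothesis in the Introduction is that youth will "be more likely to attend at least 3 mental health sessions if identified as needing services". The Data Analysis section says much the same. That is engagement among identified youth (e/b), whereas Table 2 uses e/d.

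**The concern.** Sites are randomised to waves, so what randomisation can protect is a comparison over everyone at a site, step a. Steps b, c and d form after implementation. If the app works on the first outcome, it changes who enters the denominator of the second, and then of the third and fourth. A difference in c/b, d/c or e/d may then reflect a different mix of youth rather than better or worse progression of comparable youth.

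The protocol describes its framework as one that "focuses on population-level health needs and tracks individuals across relevant stages of a health care continuum". Conditional rates used as primary effect measures do not answer a population-level question. The trial could report a decline on three primary outcomes while more youth at the site are referred, start and stay in care, or an improvement while fewer do.

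**Working it through.** **The plan's own figure.** The Primary Outcomes section states detectable differences of 2%-10% at power 0.8, two-sided α .05. It gives no baseline rates, numbers of youth or intracluster correlation, so the figure can be neither reproduced nor refuted. Over assumed baselines of 5% to 70%, and before any allowance for clustering, a 2-point difference needs about 2,213 to 9,806 youth per condition and a 10-point difference about 141 to 388. These are counts in the denominator of the step concerned. The argument below does not depend on them.

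**Inputs.** The rate definitions come from Table 2. Every progression rate below is an assumption, because the article reports none. The base is 1000 youth at step a.

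**Control condition.** 100 youth are identified, with 60% progressing at each step:
- c = 100 × 0.60 = 60; d = 60 × 0.60 = 36; e = 36 × 0.60 = 21.6.

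**App condition, case 1.** The same 100 youth progress exactly as before. A further 100 are identified and progress at 40% per step, contributing 40, 16 and 6.4:
- b = 200; c = 60 + 40 = 100; d = 36 + 16 = 52; e = 21.6 + 6.4 = 28.

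| Rate | Control | App |
|---|---|---|
| b/a | 10% | 20% |
| c/b | 60% | 100/200 = 50.0% |
| d/c | 60% | 52/100 = 52.0% |
| e/d | 60% | 28/52 = 53.8% |
| c/a | 6.0% | 10.0% |
| d/a | 3.6% | 5.2% |
| e/a | 2.16% | 2.80% |

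No youth progresses less well, yet three primary rates fall by 6 to 10 points. That is about the size of difference the trial is said to be able to detect.

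**Case 2, the app also helps.** Suppose the original 100 now progress at 65% per step, with the same 100 added at 40%. Then c/b = 105/200 = 52.5%, d/c = 58.25/105 = 55.5% and e/d = 33.86/58.25 = 58.1%. All are still below 60%.

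**Case 3, added youth progress more readily.** Suppose the added 100 progress at 70% per step, contributing 70, 49 and 34.3. Then c/b = 130/200 = 65.0%, d/c = 85/130 = 65.4% and e/d = 55.9/85 = 65.8%. All three rise although the original 100 progress no better.

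**Case 4, fewer identified.** If only 60 youth are identified and they progress at 70% per step, the counts fall to 60, 42, 29.4 and 20.6 while all three conditional rates rise to 70%.

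**Sensitivity of case 1.** Take 50, 100 or 200 added youth, progressing at 50% at each step, at 40% at each step, or at 30% then 40% and 40%. Then c/b lies between 40.0% and 56.7%, d/c between 48.6% and 57.1%, and e/d between 50.6% and 57.4%, against 60% in control. Over the same settings e/a rises from 2.16% to between 2.40% and 4.66%.

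**The hypothesis wording.** Engagement among identified youth (e/b) has the same weakness. In case 1 it falls from 21.6/100 = 21.6% to 28/200 = 14.0%.

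**Cost in precision of e/a.** Take n per condition = 2p̄(1 − p̄)(1.96 + 0.84)²/Δ², with the squared term 7.85. For 2.16% against 2.80%, p̄ = 0.0248 and Δ = 0.0064, giving about 9,270 youth. For a smaller assumed rise, 1.8% to 2.2%, p̄ = 0.020 and Δ = 0.004, giving about 19,200. Both are before clustering.

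**The case against.** Stepwise rates are a deliberate choice. The article adopts an existing cascade, and conditional rates show where youth drop out. A single rate such as e/a cannot separate better identification from better retention. That stands, and it is why the stepwise rates should be kept. It does not make them sound primary effect measures when the intervention is expected to alter their denominators.

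The site-wide rates also follow by multiplication: e/a = b/a × c/b × d/c × e/d. So a rise in engaged youth could be recovered from the planned results. But no test of e/a, c/a or d/a is set out, and the declared hypotheses concern the separate rates.

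Table 3 adds previous mental health history, where available, for the three later steps. This is a real but partial adjustment. It may be missing, and current severity is not among the covariates.

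Four stronger readings are tempting, and the documents support none of them:

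- *The added youth will be milder cases, so the three rates will fall.* Nothing says this. The app directs low scorers on its well-being questionnaire towards professional help, so added youth could have equal or greater need. Cases 3 and 4 move the other way.
- *In-app self-assessments feed step b directly.* App use is anonymous, and the cascade data come from site records. Table 3 does not say whether its self-assessments are those in the app. The point needs only the expected rise in screening.
- *No adjustment for need is planned.* The history covariate contradicts this.
- *Step-a denominators would give a purely randomised contrast.* There are two waves, and the analysis compares periods before and after implementation. Part of the contrast is within site whichever denominator is used.

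**Conclusion.** The concern holds in this form. As written, c/b, d/c and e/d compare subsets that form after implementation and whose make-up the protocol expects the app to change. They mix the app's effect with a change in who is counted, and can move in the opposite direction to the number of youth reaching each step. The rate b/a does not share this denominator problem.

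The structure follows from Table 2 and the protocol's own hypothesis of more screening. The sizes do not: shifts of 6 to 10 points in the main example rest on assumed rates, and both direction and size depend on who is additionally identified, which the documents leave open. The conditional rates can mislead; they need not.

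The mismatch between e/b in the hypothesis and e/d in Table 2 is a separate inconsistency. Settling it in favour of e/b would not remove the problem.

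**What to change.** 1. Prespecify c/a, d/a and e/a beside b/a, over all enrolled or panel youth, with the same observation window in both conditions. Name these as the measures on which effectiveness is judged.
2. Report c/b, d/c and e/d as stepwise descriptive measures, labelled as not protected by randomisation.
3. Reconcile the engagement hypothesis in the Introduction and in Data Analysis (among identified youth) with Table 2 (among those who start services).
4. Restate the 2%-10% detectable differences on the step-a scale, giving the baseline rates, numbers of youth and intracluster correlation used.

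The cost in data is nil, because the individual-level site records already planned supply every count. The cost in precision is real: later steps are small fractions of step a, and e/a may be estimated too imprecisely to show a modest gain. The step-a contrast also remains partly before versus after within site, so it still relies on the model's adjustment for time.
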